#### Cost-Effectiveness Analysis of Counseling and Reminder SMS Texts and Phone Calls

The total costs involved in implementing the interventions will be compared with the attendance of follow-up patients and the revenue generated through their follow-up sessions. The intervention costs include the salary for the team members. In addition to the costs for the phone calls and reminder SMS telecommunication charges, the cost for equipment, stationery, and the charges for utility services like water and electricity will also be included as the cost for implementing interventions. Cost effectiveness will be analyzed separately for counseling and reminders (phone calls and SMS texts) by calculating the total cost incurred per attendance of follow-up in each intervention group and the total revenue generated through the fee for the OPD ticket, investigations, medicines, and glasses provided during the follow-up visits.

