The primary objectives are to determine if parental counseling has an impact on adherence to follow-up and to determine if reminders through phone calls and SMS texts increase the follow-up rate in pediatric patients. The secondary objective is to assess the cost-effectiveness of counseling and reminder SMS texts and phone calls. We hypothesize that counseling will increase the follow-up rate from 22% to 50% and reminders through phone calls and SMS texts will increase the follow-up rate from 22% to 25% at the site of the study (mentioned in the next section).

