## Discussion

This study will reliably document not only the factors associated with follow-up rate through an intervention package (counseling and reminders through SMS texts and phone calls) but also the cost effectiveness of the intervention package. Compliance to follow-up visits is important for better outcomes of treatment for any condition. It is equally important for children with visual problems to comply with the follow-up so that they can receive complete treatment and be prevented from going permanently blind in some cases. Different studies have shown varied results regarding the effect of these interventions. Follow-up rates have found to be improved with these types of intervention in some studies while other studies show no significant improvement with the interventions [12-17]. One intervention may work better than others in some studies. We are testing these interventions to improve the follow-up rate of pediatric patients with ocular problems. Loss or noncompliance with the scheduled follow-up visits by patients who have been advised to come for follow-up is a major issue in many areas of clinical practice. Noncompliance has been a major problem with pediatric patients undergoing treatment at the Pediatric Ophthalmology Department at BEH, where only 22% of those advised attended the follow-up. Therefore, this study is attempting to determine which intervention strategy would work better for this problem. Any intervention found effective will be applied to other departments and will be implemented as the hospital policy in the future.

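### The cost-effectiveness measure is a within-group average that leaves out routine care, so each intervention is credited with visits and revenue that would have occurred anyway

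*Protocol article*

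**What the plan says.** Cost-effectiveness is the secondary objective (Protocol article, Introduction) and one of the secondary outcomes (Outcomes). The Cost-Effectiveness Analysis section fixes how it will be measured. In general terms, "The total costs involved in implementing the interventions will be compared with the attendance of follow-up patients and the revenue generated" at those visits. On the cost side, "The intervention costs include the salary for the team members", together with telecommunication charges, equipment, stationery and utilities. Each intervention is analysed on its own, by "calculating the total cost incurred per attendance of follow-up in each intervention group and the total revenue generated" from tickets, investigations, medicines and glasses.

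Numerator, denominator and revenue items are thus all stated. Routine care is not mentioned in that section, and no cost comparison with it appears elsewhere in the article.

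**The concern.** The two halves of the ratio do not match. The numerator is the cost of putting the intervention in place, which is a cost on top of routine care. The denominator counts every follow-up attendance in the group, including those that routine care would have produced. Revenue is treated in the same way.

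The article itself shows that such visits exist. The Introduction gives 22% attending at least once before any intervention, and in the second dry run (Results) two of the 13 standard-care children attended. A concurrent routine-care group is enrolled and could supply the baseline, but this analysis does not use it.

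Two things are at stake. An intervention with no effect at all would still show a finite cost per attendance and positive revenue. And because the distortion is larger for the weaker intervention, the comparison of the two can come out the wrong way round.

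**Working it through.** The cost-effectiveness section states no figure, so there is nothing to reproduce. The check compares the planned ratio with the incremental one.

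**Inputs**
- Rates: 50% counseling, 25% reminders, 22% baseline (Introduction and Sample Size).
- The 22% is attendance at one or more visits (Introduction). The primary outcome is completion of all three visits (Outcomes). The cost denominator is attendances. The control rate is therefore varied.
- Dry-run control rate: 2/13 = 15.4% (Results). The numbers are very small, so this is one more point in the range and not an estimate.
- Assumptions: one attendance per attender; arm rates held at 50% and 25%; counseling costs k times as much per child as reminders. The article gives no unit costs, so k is unknown.

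**Formulas**, with C the intervention cost per child, p the rate in the arm and p0 the rate under routine care:
- Planned ratio: C / p
- Incremental ratio: C / (p − p0)
- Understatement by the planned ratio: p / (p − p0)

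The last factor exceeds 1 whenever 0 < p0 < p, and it grows as p falls towards p0. That is why the weaker arm gains more. The same algebra holds if p and p0 are replaced by mean attendances per child, so the direction does not depend on the one-attendance assumption.

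**Break-even cost ratio**
- Planned: reminders look cheaper once k > 0.50/0.25 = 2.0, whatever the control rate.
- Incremental: reminders are cheaper only if k > (0.50 − p0)/(0.25 − p0).

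| Control rate p0 | Understatement, counseling | Understatement, reminders | Incremental break-even k |
|---|---|---|---|
| 5% | 0.50/0.45 = 1.11 | 0.25/0.20 = 1.25 | 0.45/0.20 = 2.25 |
| 10% | 0.50/0.40 = 1.25 | 0.25/0.15 = 1.67 | 0.40/0.15 = 2.67 |
| 15% | 0.50/0.35 = 1.43 | 0.25/0.10 = 2.5 | 0.35/0.10 = 3.5 |
| 2/13 | 0.50/0.346 = 1.44 | 0.25/0.096 = 2.6 | 0.346/0.096 = 3.6 |
| 20% | 0.50/0.30 = 1.67 | 0.25/0.05 = 5.0 | 0.30/0.05 = 6.0 |
| 22% | 0.50/0.28 = 1.79 | 0.25/0.03 = 8.33 | 0.28/0.03 = 9.33 |

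The ranking reverses when k lies between 2.0 and the last column. The window is open for any control rate above 0 and below 25%, but it is narrow when that rate is low.

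**Example with an assumed k = 3 and a reminder cost of 1 unit per child.** The planned ratios are 3/0.50 = 6.0 for counseling and 1/0.25 = 4.0 for reminders, so reminders look cheaper. Incrementally:
- control 22%: 3/0.28 = 10.7 against 1/0.03 = 33.3, reversed;
- control 15%: 3/0.35 = 8.6 against 1/0.10 = 10.0, reversed;
- control 10%: 3/0.40 = 7.5 against 1/0.15 = 6.7, not reversed.

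**No-effect case.** In the dry run, counseling and standard care each had 2 attenders of 13. The additional attendance is zero and the incremental ratio is undefined, yet the planned ratio is 13C/2 = 6.5C. This shows how the measure behaves and says nothing about the interventions.

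**The case against.** The strongest reply concerns size and consequence. It accepts that the formula omits routine care.

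First, a reader might infer that the plan's method reverses the ranking for every cost ratio from 2.0 to 9.3, and understates the reminder cost eightfold. The documents do not support that as a general result. Those figures rest on a 3-point difference between 25% and 22%, with a 22% that measures attendance at one or more visits and not three-visit compliance or a count of attendances. A compliant child contributes three attendances, a partly compliant child one or two, and late visits are also recorded (Record Maintenance). The article gives no expected attendance counts per group and no unit costs, so whether k falls inside any window is unknown. This stands, and it is why a range is shown.

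Second, a reader might infer that the hospital would adopt the wrong intervention. The Discussion says: "Any intervention found effective will be applied to other departments and will be implemented as the hospital policy in the future". That ties adoption to effectiveness, which is judged across all three groups, and not to cost per attendance. At 25% against 22% with 264/3 = 88 per group, the standard error is √(0.25×0.75/88 + 0.22×0.78/88) = 0.064. The standardised difference is 0.03/0.064 = 0.47, against a critical value of 2.39 at 0.05/3, which gives power of about 3%. A near-null intervention would seldom be declared effective, so its flattering cost ratio would seldom bear on adoption. This also stands. The measure matters most when both interventions work and cost helps to choose between them, and there the distortion is smaller.

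Neither reply removes the defect. Nor is this a detail left to a fuller document, because the article itself fixes the ratio.

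**Conclusion.** The point holds. Followed as written, the plan credits each intervention with baseline visits and revenue, understates the cost per additional attendance, and favours the weaker intervention. That direction needs only some attendance under routine care and a higher rate in the arm.

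The size is illustrative. With arm rates of 50% and 25%, the upper end of the reversal window runs from 2.25 at a 5% control rate to 9.33 at 22%, and its lower end stays at 2.0. A reversal is possible but not established, because k and the control rate on the relevant measure are unknown. The primary outcome and its analysis are unaffected. The change should be made because cost-effectiveness is a stated objective and, in the Abstract, a headline conclusion.

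**What to change.** For each intervention, report the difference from routine care per allocated child in:
- cost;
- attendances, or the compliance proportion, counted in the same way in every group;
- revenue, where the fees for control-group visits can be retrieved.

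Give each difference with its uncertainty. Salaries, equipment and utilities are largely group-level costs, so their uncertainty is better shown by varying the inputs than by resampling children.

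Report an incremental cost per additional attendance only when the attendance difference is clearly positive. With a difference near zero the ratio is unstable and its interval cannot be interpreted, so the separate differences should carry the result. Keep the within-group cost per attendance as a description.

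The cost is modest. Follow-up is already recorded for all three groups (Record Maintenance), so the attendance part is a change of formula. The revenue part needs the same fee items extracted for control-group visits, and the article does not say that these will be collected. The reported figures will look less favourable, and for a weak intervention there may be no ratio to report.

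### The revenue comparison sets intervention cost against gross sales, including medicines and glasses, without deducting what those goods cost the hospital, so it overstates the financial return

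*Protocol article*

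**What the plan says.** The Introduction gives the economic question the standing of an objective: "The secondary objective is to assess the cost-effectiveness of counseling and reminder SMS texts and phone calls".

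The section on cost-effectiveness analysis in the Methods then describes what is compared: "The total costs involved in implementing the interventions will be compared with the attendance of follow-up patients and the revenue generated through their follow-up sessions".

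- **Cost side.** The section states that "The intervention costs include the salary for the team members". It adds telecommunication charges, and then "the cost for equipment, stationery, and the charges for utility services like water and electricity will also be included as the cost for implementing interventions".
- **Return side.** The quantity is "the total revenue generated through the fee for the OPD ticket, investigations, medicines, and glasses provided during the follow-up visits".
- **Effectiveness measure.** Each intervention is also to be assessed by "calculating the total cost incurred per attendance of follow-up in each intervention group", which does not use revenue.

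Neither this section nor the rest of the article mentions net revenue, a margin, or a deduction for goods supplied. The section gives no threshold and no formula for combining cost with revenue.

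**The concern.** The two sides of the comparison do not have the same scope. Revenue takes in the full price of medicines and glasses sold at follow-up visits. The cost side is confined to delivering the intervention, and stock bought for resale is not a cost of counseling a family or sending a reminder. The purchase cost of the goods is therefore counted nowhere, while their sale price is counted in full.

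A reader who sees revenue above intervention cost will naturally conclude that the intervention pays for itself. That conclusion can be wrong in sign, and the error always favours the intervention. Cost-effectiveness is the stated secondary objective, and the abstract's conclusions offer the economic result for use in all departments of the hospital, so a flattering figure could be read widely.

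**Working it through.** **Stated figure.** The article gives no cost, price, revenue or margin, so there is nothing to reproduce. The check is a reading of the text plus an accounting identity.

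**Inputs**
- C: cost of implementing one intervention, with the components listed in the cost-effectiveness section.
- R: gross revenue from that group's follow-up visits, as defined in the same section.
- c: share of R that the hospital spends on supplying the items sold and that is not already in C. The article does not give it, so every value below is an assumption.

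**Formulas**
- Apparent surplus, taking the natural difference between the two quantities: R − C.
- Surplus after supply cost: R(1 − c) − C.
- Overstatement of the surplus: (R − C) − [R(1 − c) − C] = cR, which is never negative.
- The sign reverses when R > C and R(1 − c) < C, that is, when c > 1 − C/R.

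**Illustration with assumed values, C = 100 throughout**

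| R | Apparent surplus | Net, c = 0.2 | Net, c = 0.4 | Net, c = 0.6 | Break-even c |
|---|---|---|---|---|---|
| 110 | +10 | −12 | −34 | −56 | 0.09 |
| 125 | +25 | 0 | −25 | −50 | 0.20 |
| 150 | +50 | +20 | −10 | −40 | 0.33 |
| 200 | +100 | +60 | +20 | −20 | 0.50 |

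For R = 150 the break-even share is 1 − 100/150 = 0.33. At c = 0.4 the net position is 150 × 0.6 − 100 = −10, against an apparent +50.

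**Ratio scale.** Gross revenue exceeds net revenue by a factor 1/(1 − c). For assumed shares of 0.3, 0.5 and 0.7 this is 1/0.7 = 1.43, 1/0.5 = 2.0 and 1/0.3 = 3.33. An intervention with a gross revenue-to-cost ratio between 1 and that factor would appear to cover its cost without doing so.

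**Cost per attendance.** This is C divided by the number of attendances. Neither R nor c enters, so it is unchanged.

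**The case against.** **The article is a condensed account, and costing detail may sit in the full protocol.** This would answer a complaint about a missing detail. Here the article states both sides of the comparison and calls the revenue total. If a fuller document nets it off, the article's text still needs correcting.

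**There is no rule to be wrong.** This is right as far as it goes. The section says that costs will be compared with revenue. It writes no subtraction, ratio or pass mark, and R − C is only the obvious way to carry out the comparison. The fault lies in what is compared.

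**The cost list may be wider than it looks.** This stands in part. The salary sentence is open-ended and the team members are not defined. The study roles include a pediatric ophthalmologist (Study Procedure) and an optometrist (Data Entry and Validation), and equipment and utilities are listed. Some consultation and investigation cost may therefore already be counted, and deducting it again would count it twice. None of these headings naturally covers medicines and glasses bought for sale.

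**Stronger readings that the documents do not support**
- *The revenue result will decide hospital policy.* The Discussion says "Any intervention found effective will be applied to other departments and will be implemented as the hospital policy in the future". This ties adoption to effectiveness, and nothing in the article makes revenue a criterion.
- *The ranking of the two interventions will be reversed.* With a common c, both revenue-to-cost ratios shrink by the same factor (1 − c) and keep their order. Reversal on that scale needs item-cost shares that differ between groups. On the difference scale it needs differing shares or unequal intervention costs. The article gives no shares and no costs.
- *The net figure is the true return on the intervention.* It is not. The section uses total revenue in each intervention group and does not subtract what standard care yields. Netting off supply cost removes one error and leaves that one.

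**Conclusion.** The point holds for medicines and glasses. Compared as written, intervention cost is set against gross sales of goods whose purchase cost is left out, and the financial return is overstated by cR. An apparent surplus is a net loss whenever R > C and c exceeds 1 − C/R.

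The direction is certain for any positive supply cost. The size is unknown, because the article gives no prices or margins and every figure in the illustration is assumed. For investigations the point is weaker, since part of their cost may already fall under salaries or equipment. The cost-per-attendance analysis is sound in this respect. The flaw is confined to the revenue comparison within a secondary objective, and it can be corrected before analysis.

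**What to change.** In the cost-effectiveness section, replace total revenue with net revenue: receipts from the outpatient ticket, investigations, medicines and glasses, minus the hospital's purchase cost of the medicines and glasses and any direct investigation cost not already included under salaries or equipment. State which staff the salary item covers, so that nothing is deducted twice. Compare this net figure with intervention cost.

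If the item costs cannot be obtained, report revenue descriptively, label it as gross, do not set it against intervention cost, and rest the cost-effectiveness conclusion on the cost per attendance that is already planned.

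The cost is a change of wording and a lookup of purchase costs. That the hospital can supply them is an assumption: the article mentions an optical dispenser or pharmacist but not who holds the price records. Enrolment, allocation and patient contact do not change. The stated return will be less favourable.

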### Ethical Approval

The ethical approval has been obtained from Ethical Review Board (ERB) of the Nepal Health Research Council (ERB protocol registration #761/2020 P). The data collection was initiated on January 24, 2021, but due to the COVID-19 pandemic, as of September 2021, we have only been able to enroll 154 of the 264 participants (58.3% of the sample size).

## Results

Descriptive statistics will be presented, and demographic variables will be summarized by computing means with SD for continuous variables and proportions for categorical variables. Associations between sociodemographic variables and compliance rates will be presented. The associations will be computed using categorical variables. Two dry runs were conducted to assess the logistics and flow of participants. The first dry run was conducted by taking only 10 patients who were not the actual study participants, but the second dry run was conducted with the actual participants as per the inclusion and exclusion criteria. A total of 38 study participants were enrolled for a duration of 1 month for the second dry run. Of these participants 13, 13, and 12 were divided into the standard care group, counseling group, and reminder with SMS texts and phone call groups, respectively. The mean age of the children was 3.71 (SD 0.61) years, with a range of 0.07 to 14 years. There were more male children 24 (63.16%) as compared to female children 14 (36.84%). Most of the children were of Aryan descent (63%), and more than 80% of the children were accompanied by their mother. Only 7 out of the 38 patients attended the follow-up visit. All those who attended have attended only the first follow-up visit. Three participants were from reminder group, two were from the counseling group, and two were from the standard care group. Out of the 38 children, 14 (36.8%) were diagnosed with congenital naso-lacrimal duct obstruction and 7 with amblyopia, with the others having conjunctivitis, eye injury, corneal ulcer, or squint.

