### Outcomes

The primary outcome is the proportion of children completing all 3 follow-up visits in the routine standard care group, counseling group, and reminders through SMS texts and phone call group.

The secondary outcomes include the effect of parental or guardian education status in compliance to follow-up, the visual status of the children in subsequent follow-up visits, the effect of traveling distance and cost in compliance to follow-up, and the cost-effectiveness of the intervention.

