### Independent Variables

The independent variables will include the following sociodemographic factors: gender, age, ethnicity, educational status, occupation of parent or guardian, attendant relationship with the child (of parent or guardian attending with the child), distance traveled, and cost for the travel to the hospital.

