#### Multivariate Analysis

Multivariate logistic regression analysis will be performed to adjust for the simultaneous effects of multiple factors on the outcome variable. The criteria for inclusion of factors in the multivariate analysis are to include all variables from the univariate analysis with a *P* value of .1 along with all the variables of known importance. To assess the importance of each variable included in the model, the Wald statistic for each variable will be used.

Before the multivariate analysis is conducted, the association among independent variables will be checked by a chi-square test. For independent variables having more than 2 categories, dummy variables will be created. All the variables meeting the above selection criteria will be entered one by one, starting with the highly significant factors from the univariate analysis. The overall significance of independent variables in the model will be assessed by likelihood ratio test (G statistic). Selection of the final model will be based on parsimony, biological interpretability, and statistical significance. The parameters of the logistic regression model will be estimated by the maximum likelihood method. The adjusted ORs and their 95% CIs will be computed using the estimates of parameters of the final model. The dependent variable will be dichotomous: either compliance with the follow-up instruction has increased, or it has remained changed (no difference) from before the intervention study to after it. The final model will be tested for goodness of fit by Hosmer- Lemeshow chi-square (*Χ*^2^) statistic. *P* values will be noted to assess the model fit. Imputation and intention to treat analysis will also be conducted (if required).

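### Associations with compliance are committed to categorical variables, which would lose information on travel distance and cost (a secondary outcome) and on age (a covariate) wherever these are recorded as numbers

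*Protocol article*

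**What the plan says.** Four places in the protocol article bear on this.

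- **Results.** "Associations between sociodemographic variables and compliance rates will be presented", followed directly by "The associations will be computed using categorical variables". The same paragraph recognises continuous variables, but for description: "demographic variables will be summarized by computing means with SD for continuous variables and proportions for categorical variables".
- **Independent Variables.** "The independent variables will include the following sociodemographic factors: gender, age, ethnicity, educational status, occupation of parent or guardian". The list ends with "distance traveled, and cost for the travel to the hospital". Age, distance and travel cost are therefore all sociodemographic factors in the article's own terms.
- **Outcomes.** The secondary outcomes include "the effect of traveling distance and cost in compliance to follow-up". Age is in no stated outcome.
- **Multivariate Analysis.** Associations among the independent variables are checked by chi-square, and "For independent variables having more than 2 categories, dummy variables will be created". Variables reach the multivariable model through a univariate P value of .1 or because they are of known importance.

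**The concern.** Logistic regression accepts a numeric predictor as it stands. Cutting it into two, three or four groups treats children at opposite ends of a group as identical, and three or more groups also cost extra degrees of freedom. If distance and cost are numeric, the stated method makes a real gradient with compliance harder to detect, and that gradient is what a secondary outcome asks about. A weakened variable is also more likely to miss the P .1 screen.

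Age and distance also matter as adjusters. Under Study Procedure, children are assigned by fixed rotation rather than at random, so adjustment carries some weight, and coarse categories adjust less completely. I have not quantified that part.

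**Working it through.** **1. The plan's own figure.** The article gives no power for covariate associations, only the total of 264. Inputs from Sample Size: 50% against 25%, two-sided alpha 0.05/3 = 0.0167, 80% power, 10% loss.

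n = [2.394 × √(2 × 0.375 × 0.625) + 0.842 × √(0.25 + 0.1875)]² / 0.25² = 77.1, so 78 per group. 78/0.9 = 86.7, so 87 per group, and 3 × 87 = 261. This is close to 264, so 264 is used below. Nothing in this point changes it.

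**2. Information kept after cutting.** For a normal predictor in k equal groups, the share of variance kept is (1/k) Σ mᵢ², where mᵢ is the group mean.

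- k = 2: mᵢ = ±2 × 0.399 = ±0.798, so the share is 0.637 (= 2/π).
- k = 3: 0.793.
- k = 4: 0.861.

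**3. Power by formula.** The noncentrality for a continuous term is about N × p(1−p) × β², with β the log OR per SD. Assumed, not in the article: p = 0.30, β = 0.4 or 0.3, linear on the logit scale.

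- β = 0.4: 264 × 0.21 × 0.16 = 8.87. Continuous: Φ(√8.87 − 1.96) = Φ(1.02) = 85%. Median split: 8.87 × 0.637 = 5.65, Φ(2.38 − 1.96) = 66%.
- β = 0.3: 264 × 0.21 × 0.09 = 4.99. Continuous: Φ(2.23 − 1.96) = 61%. Median split: 4.99 × 0.637 = 3.18, Φ(1.78 − 1.96) = 43%.

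Tertiles keep more information (0.793) but use 2 degrees of freedom, and end in about the same place.

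**4. Power by simulation.** Likelihood ratio tests, N = 264, 30% compliance, normal predictor, quantile cuts:

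| Log OR per SD | Level | Continuous | Median split | Tertile dummies |
|---|---|---|---|---|
| 0.4 | .05 | 85% | 66% | 65% |
| 0.3 | .05 | 61% | 43% | 42% |
| 0.4 | .1 (screen) | 90% | 75% | 76% |
| 0.3 | .1 (screen) | 70% | 55% | 53% |

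Repeat simulations agree within about 3 points.

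**5. Other assumptions, 5% level.**

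- *Compliance 32%* (mean of the article's 22%, 50% and 25%), log OR 0.41 in size (OR about 0.66 per SD): continuous 84%; median split, tertiles and quartiles 67%, 68% and 65%.
- *Same, right-skewed (exponential) predictor*, plausible for distance and cost: 79% against 52%, 54% and 54%.
- *Same, N = 237* (264 less 10%): normal 85% against 65%, 63% and 59%; skewed 72% against 47%, 45% and 46%.
- *Compliance 15%*, log OR 0.4: 63% against 45% (median split) and 42% (tertiles). A low value is worth testing because none of the 38 children in the second dry run had gone beyond the first follow-up visit.
- *True effect a step at about the upper third*: tertile dummies beat the linear term, 74% against 68% (log OR 0.4) and 49% against 44% (0.3).

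**The case against.** The strongest reply is that no passage names age, distance or cost as variables to be cut. The sentence in Results is general. The dummy-variable rule is conditional and is ordinary coding for ethnicity, education or occupation. This stands as a caution: the point is inferred from Results read with Independent Variables. It does not remove the point, because the sentence directly follows one about sociodemographic variables, the three are on that list, and no passage provides for a continuous term.

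Second, only age is shown to be numeric (mean 3.71 years, range 0.07 to 14). Distance and cost are recorded in the proforma, which is not shown. If they were collected in bands, the information is lost at collection and not in the analysis. This stands and makes the point conditional.

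Third, the P .1 screen is not the only way into the model. The Introduction cites a study that found distance and cost to be major barriers, so both could enter as variables of known importance. This softens the screening argument but leaves the loss of power.

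Fourth, the size depends on the shape of the effect, as the step scenario shows. This stands.

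A reader might also infer that cutpoints will be chosen after seeing the data, because none is given. The article does not support that: cutpoints may be in the full protocol or analysis plan, and their absence here is no finding.

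**Conclusion.** The point holds in a limited form. The article states a method, so this is not a detail left to another document, and the method would put distance, travel cost and age into categories. Distance and cost bear on a stated secondary outcome. Age is an adjustment covariate only, and it would be wrong to say that all three answer secondary outcomes.

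With 264 children, about 30% compliance, a linear logit effect and log OR 0.3 to 0.4 per SD, categorising costs about 18 to 20 percentage points of power at the 5% level (85 − 65 = 20; 61 − 43 = 18). It costs about 14 to 17 points at the P .1 screen (90 − 76 = 14; 70 − 53 = 17). A skewed predictor loses more, up to about 27 points (79 − 52). A step effect near a cutpoint can reverse the loss. Apart from the 264, these inputs are assumptions.

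It might be inferred that the trial's main result is weakened. It is not, directly: the three-group comparison of children completing all follow-up visits and the sample size do not depend on how these variables are coded. The point is minor and worth making because the change is cheap.

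**What to change.** Replace the sentence in Results with one saying that age, distance traveled and travel cost, where recorded as numbers, enter the univariate and multivariable logistic models as continuous terms. Use a log scale for distance and cost if they are skewed, and check for non-linearity, for example with a spline, which also guards against a step-like effect. Keep categories for descriptive tables. In Multivariate Analysis, limit the chi-square check among independent variables to those that are categorical by nature, and use correlations or rank methods for the rest.

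The cost is a little more analysis work and no change to N. If the proforma records distance or cost in bands, numeric values would have to be captured for the participants still to be enrolled; 154 of 264 had been enrolled by September 2021. Children already recorded in bands would stay in bands unless the values can be recovered.
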